#### tDCS

The administration of tDCS involves using the Soterix 1x1 platform and 5 cm × 5 cm electrodes. The anode is positioned over the left frontal lobe at F7 according to the 10-20 electrode placement system, while the cathode is placed extracephalically over the right cheek. This unihemispheric tDCS montage aims to achieve more targeted stimulation, aligning with predictions from prior modeling studies (Moliadze et al., 2010; Wagner et al., 2007; Bhattacharjee et al., 2019). While the F7 position provides a standardized landmark for left IFG stimulation, it is important to acknowledge that individual anatomical differences such as cortical folding, sulcal depth, and skull thickness can influence the intensity and distribution of the electric field delivered to the target region (Laakso et al., 2015; Saturnino et al., 2019). However, modeling data in neurodegenerative populations suggests that such variability may not substantially compromise targeting, despite atrophy-related anatomical changes in individuals with PPA, consistent current flow patterns to target regions remained consistent across variants and individuals (Unal et al., 2020). While individual electric field modeling can improve focality, it remains resource-intensive and challenging to implement in large clinical trials. Moreover, in the context of neurodegenerative conditions like PPA, where functional reorganization and loss of network hubs may occur, increased focality may not always be advantageous (Mandelli et al., 2018; Agosta et al., 2014; Tao et al., 2020). In fact, when comparing conventional and high-definition tDCS, conventional tDCS seems to yield stronger effects, and it could be the lack of focality that make it very efficacious as it is discussed in Unal et al. (2020). These findings support the robustness of this tDCS montage in achieving reliable stimulation even in the presence of disease-related anatomical variability. See Figure 3 for the simulation of current propagation with the montage used in this study.

**Figure 3 F3:**
[figure not shown]
Electric field simulation of the tDCS montage created using SimNIBS 4.1.0 (Thielscher et al., 2015). The montage places the anode over the left inferior frontal gyrus (IFG) at the F7 location and the cathode extracephalically on the right cheek. The simulation visualizes current propagation and electric field intensity, with targeted stimulation of the left IFG. The color map represents the magnitude of the electric field (MagnE) in volts per meter (V/m).

To minimize skin-electrode reactions, a non-metallic, conductive rubber electrode with a saline-soaked sponge is used to cover the left inferior frontal gyrus (IFG). Each tDCS session delivers 2 mA of current (with an estimated current density of 0.08 mA/cm^2^) for 20 min during the a-tDCS period, concurrent with the naming therapy, and is followed by at least 25 min of therapy alone or the time required to complete the trained list.

During sham stimulation (s-tDCS), a brief 30-s ramp-up and ramp-down of current mimic the sensation of active tDCS. This method has effectively blinded participants to the stimulation condition in prior studies (Palm et al., 2013). In earlier studies conducted by our team, including randomized, sham-controlled trials of tDCS in individuals with PPA, blinding procedures were shown to be effective. Specifically, post-trial assessments of participant and care partner guesses regarding stimulation condition (active vs. sham) revealed accuracy rates at chance (Tsapkini et al., 2018) or were unable to identify a difference (Roncero et al., 2019), suggesting successful blinding in this population.

To monitor adverse effects, each participant is asked to rate their pain level once at the end of each stimulation session using the Wong-Baker FACES Pain Rating Scales (http://www.WongBakerFACES.org) (Wong-Baker FACES Foundation, 2022). The protocol requires each participant to undergo 15 consecutive weekday sessions.

After completing the trial, at T7, participants will also be asked to indicate during which period they believe they received active or sham stimulation (using a dichotomous response format). This protocol ensures comprehensive data collection while maintaining participant safety and minimizing potential sources of bias.

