#### Lifelong experiences and lifestyle

Similar to genetic factors and biomarkers, lifelong language experiences, such as bilingualism, and lifestyle factors, including exercise and sleep habits, have been argued to influence cognitive reserve and neural plasticity, thereby affecting the efficacy of therapy. For example, bilingual individuals with post-stroke aphasia have been shown to benefit more from therapy and have better recovery than their monolingual peers (Masson-Trottier et al., 2022; Lahiri et al., 2021). However, to our knowledge, bilingualism in individuals living with PPA has not been investigated as a predictor of therapy outcomes (Norhan et al., 2023). Exercise has also proven to maintain and potentially improve cognitive functions in aging (Krivanek et al., 2021) and individuals with post-stroke aphasia (Lorenzen and Murray, 2008). Understanding the interplay between these factors and therapy outcomes could provide valuable insights for optimizing treatment approaches and enhancing clinical care for individuals with PPA.

In summary, studies focusing on behavioral treatment of common symptoms in individuals living with PPA, such as anomia and agraphia, have shown promising results in terms of improvements in trained items immediately following intervention, as well as generalization to untrained items and retention of therapy gains weeks after the intervention ends (Robinaugh and Henry, 2022; Taylor-Rubin et al., 2021; Cadorio et al., 2017; Wauters et al., 2023). Neuromodulation methods, especially tDCS, have further enhanced these outcomes, promoting the maintenance and generalization of language behaviors (Cotelli et al., 2020; Coemans et al., 2021; Nissim et al., 2020). However, a Phase II multisite study has yet to be performed to evaluate large-scale efficacy and further assess safety, examining the benefits of tDCS in individuals with PPA. Furthermore, predicting therapy outcomes in PPA remains complex, influenced by factors such as PPA variant, neuroanatomical and neurofunctional factors, and baseline cognitive abilities. Significant gaps remain in understanding the roles of genetic factors, biomarkers, and lifelong language experiences in shaping therapeutic outcomes, particularly with tDCS. Addressing these gaps is important for optimizing treatment approaches and improving clinical care and neuromodulation outcomes for individuals with PPA.

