### Randomization and blinding

As shown in Table 1, following the T1 assessment, participants will be randomly allocated to either Group 1 or Group 2, thereby determining the order of stimulation conditions. Randomization is performed independently for each variant (lvPPA and nfvPPA), employing block randomization with blocks of four participants, and each site performs randomization independently. Within each block, two individuals will be assigned to Group 1 and the other two to Group 2, ensuring balanced allocation across treatment arms within each PPA variant. Randomization ensures a balanced allocation of treatment sequences across participants, thereby controlling for potential order effects and minimizing biases associated with the crossover design (such as period effects and potential carry-over effects, although limited in this study by the washout period of 3 months (Li et al., 2015; Piantadosi, 2024).

Following the allocation, each participant will be assigned 15 unique five-digit codes provided by the manufacturer of the tDCS stimulator upon device programming (one for each intervention day), indicating whether they receive active stimulation (a-tDCS) or placebo (s-tDCS). The codes are necessary to initiate the tDCS delivery device, but do not reveal whether active or sham stimulation is administered. The research team (including therapists and assessors) and participants will be blinded to whether a- or s-tDCS is being administered during each period to maintain a fully blinded study design. The code list will be decrypted upon study completion to identify when each participant received a- and s-tDCS. The specific programming of the tDCS device during the s-tDCS period condition can be found in the tDCS section below.

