#### Exclusion criteria

We will exclude individuals who have any of the following: a history of neurological disease, including vascular dementia, large vessel stroke, or attentional deficit; uncorrected hearing loss or visual acuity loss; a history of major pre-morbid psychiatric disorders; left-handedness; or advanced dementia impairments [Mini-Mental State Examination (MMSE) (Folstein et al., 1975) < 15] or severe language impairments preventing the participation in assessments and therapy.

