**Figure 2 F2:**
[figure not shown]
The flow of NaSp therapy.

As shown in Table 1, Figure 1, a therapist will administer therapy 5 days per week for three consecutive weeks. Therapy will last between 45 and 90 min, including the concomitant stimulation during the first 20 min. The exact duration of therapy will vary depending on the participant's tolerance for effort and speed of execution, and breaks will be taken if needed. Therapy will be conducted individually, in person, in a quiet room.

During each therapy session, the 20 words on the trained list (described in the next section) will be used for that period. To ensure therapy validity across different sites, a NaSp app was developed by the first author ([name]) in R using Shiny App. The app guides the therapist in following the NaSp flow according to the participant's answers. It allows the therapist to track the participant's spoken and written naming performance, as well as the effectiveness of cues when used. A comprehensive NaSp tutorial was also developed to help train therapists at the different sites.

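### The one procedure the article gives for monitoring adverse effects of stimulation is a pain rating, which cannot register painless effects such as itching, tingling, dizziness or skin redness

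*Protocol article*

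**What the plan says.** The relevant text is in the protocol article under Interventional methods, tDCS, in the paragraphs that follow Figure 3. Adverse-effect monitoring is described in one sentence: "To monitor adverse effects, each participant is asked to rate their pain level once at the end of each stimulation session". The instrument named is the Wong-Baker FACES scale.

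The same paragraphs mention two effects of stimulation that need not be painful. On the skin: "To minimize skin-electrode reactions, a non-metallic, conductive rubber electrode with a saline-soaked sponge is used". On sensation, in describing the sham: "a brief 30-s ramp-up and ramp-down of current mimic the sensation of active tDCS". The first is about prevention and the second about blinding; neither comes with a way of recording the effect. The section ends by asserting that data collection is thorough and that participants are kept safe.

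Three other places bear on the point:

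- **Second electrode site.** The anode is at F7, and "the cathode is placed extracephalically over the right cheek".
- **Blinding.** "The research team (including therapists and assessors) and participants will be blinded".
- **Rationale.** The Introduction says that "a Phase II multisite study has yet to be performed to evaluate large-scale efficacy and further assess safety".

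**The concern.** The article is not silent on adverse effects. It states what it wants to monitor and fixes the instrument. That instrument has one dimension, pain, while the effects of interest include some that do not hurt. A painless effect leaves the rating at its lowest level however often it is asked.

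What is at stake is the tolerability information the trial can report. The crossover gives every completer both conditions, so active and sham could be compared within person. With the procedure described, that comparison covers pain and nothing else.

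Asking directly is also worth more here than in most trials. All participants have a language disorder, and the related exclusion covers only "severe language impairments preventing the participation in assessments and therapy". People who remain eligible may under-report a mild, painless effect unless someone asks. That is a reasonable inference about the population; the article does not report it as a finding.

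**Working it through.** The article gives no figure to reproduce. The check has two parts: whether the tool covers the purpose, and what the remedy costs.

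**Coverage.**

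1. Purpose stated in the tDCS section: monitor adverse effects.
2. Tool stated in the same sentence: a pain rating, once per stimulation session.
3. Test: can a non-painful effect change the recorded value? For itching, tingling, dizziness or redness without pain, the correct answer on a pain scale is no pain. The record is then the same as for a participant with no effect at all.
4. Search for anything in the article that fills the gap:
   - Data collection and Outcome measures list language, cognitive and questionnaire measures, MRI, genetics and blood biomarkers. None is presented as monitoring of stimulation effects.
   - Statistical analysis describes no safety or tolerability analysis.
   - The question at T7 about which period was active is a check on blinding.
5. Result: in the text shown, no procedure records a painless effect of stimulation.

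**Cost of a short checklist.** The inputs are 15 sessions per period and two periods (Trial design and settings, Figure 1), and the session length from the NaSp therapy section: "Therapy will last between 45 and 90 min, including the concomitant stimulation during the first 20 min". The time per checklist is assumed to be 2 minutes, with a range of 1 to 3.

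- Sessions per completer: 15 × 2 = 30.
- Checklist time: 30 × 2 = 60 min (range 30 × 1 = 30 to 30 × 3 = 90 min).
- Therapy time: 30 × 45 = 1,350 min to 30 × 90 = 2,700 min.
- Share at 2 minutes: 60 / 2,700 = 2.2% to 60 / 1,350 = 4.4%.
- Share over the whole assumed range: 30 / 2,700 = 1.1% to 90 / 1,350 = 6.7%.

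**The case against.** The strongest reply is that this is a condensed article. Event definitions, event logs and serious-event reporting normally sit in the full protocol, and the detailed schedule is in a supplement that is not shown. The article nowhere says that the pain rating is the sole record. If a routine event log exists, the faces scale is an extra item that suits people with aphasia because it needs little language. This stands. A reader might infer that the trial collects no other safety data; the article does not support that, and it is not claimed here. What remains is narrower: where the article does specify a method for this purpose, the method measures one kind of effect.

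A second reply is that safety is not an aim. The phrase about further assessing safety describes a gap in the literature, and the Objectives section sets efficacy and prediction aims only. This also stands and limits the point to tolerability data.

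A third reply concerns blinding. Therapists and participants are blinded, everyone passes through both conditions, and prompting about sensations or having a therapist note the skin after every session draws attention to cues that might differ between active and sham. Withholding the form from assessors does not remove this. It is a real cost and it shapes the fix below, but it is small. The sham is built to imitate the sensation, and the tDCS section cites the team's earlier trials, in which guesses were at chance or no difference could be identified.

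A reader might also try to size the problem from the much longer current-on time in the active period, or by counting which effects named in the section go unrecorded. Neither works. Exposure time would be the same under any monitoring tool and measures no missed effects. The sentences on skin and sensation serve other purposes and are not a promised list of safety items.

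**Conclusion.** The point holds in limited form and is minor. The procedure the article gives for monitoring adverse effects records pain intensity only, so painless effects of stimulation would go unrecorded by it. The consequence is confined to tolerability information; the primary and secondary efficacy analyses do not depend on it.

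The conclusion rests on the text shown and is held with medium confidence, because the full protocol and the detailed schedule could contain a broader procedure. The number of effects that would be missed cannot be estimated from the article, and no magnitude is claimed beyond the cost of the remedy.

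**What to change.** Keep the faces scale. After each stimulation session, in both periods and with identical wording, add a brief yes/no checklist supported by pictures. It should cover non-painful effects (itching, tingling, dizziness) and ask one question about any skin problem under either electrode, at F7 or on the right cheek. Keep the items few, since several similar sensation words may be hard for some participants.

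Do not ask the therapist for a routine skin note. Have one made only if the participant reports a problem or a reaction is evident when the electrodes come off. This limits the attention drawn to condition cues.

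Record the checklist on one added form in REDCap, which the trial already uses. Keep it from the outcome assessors and tabulate the answers by condition after unblinding. If the full protocol already provides for this, a citation in the article settles the point.

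The cost is the session time worked out above, one data form, and a small residual risk to blinding of participants and therapists.

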### Outcome measures

Each site has designated assessors trained to use the materials developed for this RCT to standardize assessments across sites. These materials include an assessment manual, a dynamic Microsoft PowerPoint presentation (referred to as the *Assessment Presentation*), and a scoring sheet booklet. As shown in Table 1, Figure 1, assessments are repeated seven times over a period of 33 weeks. All assessment tasks are organized in these materials in the order of administration and divided into four balanced working blocks. The assessments can be completed over two full days or across four half-days within a week.

All participant instructions are integrated into the Assessment Presentation and appear on the scoring sheets, along with additional administration details as necessary. The timing constraints are embedded in the presentation for tasks with time limits to ensure consistent administration throughout each site involved. The assessment manual includes further scoring guidelines, task-specific details, and an FAQ section for each task. Inter-site meetings are organized as needed to discuss scoring questions, and the decisions are documented in the assessment manual.

Finally, all assessment data will be collected and managed using REDCap electronic data capture tools hosted at Johns Hopkins University (Harris P. A. et al., 2019; Harris et al., 2009). REDCap (Research Electronic Data Capture) is a secure, web-based software platform designed to support data capture for research studies, providing (1) an intuitive interface for validated data capture; (2) audit trails for tracking data manipulation and export procedures; (3) automated export procedures for seamless data downloads to standard statistical packages; and (4) procedures for data integration and interoperability with external sources.

#### Primary outcome measures

The primary outcome measure will be the change in performance between time points, as measured by phonemic accuracy (during spoken naming) and letter accuracy (during spelling) of trained items. Phonemic and letter accuracy will be calculated on a scale of 0–100%, with a higher number reflecting higher accuracy, using the Phonology analysis and Spelling analysis tools in Open Brain AI (Themistocleous, 2023).

At each assessment time point, participants undergo a comprehensive evaluation that includes the NaSp spoken naming and spelling task, which serves as the primary outcome measure. The task consists of 80 stimuli corresponding to the Level 1 stimuli previously outlined in the Therapy Stimuli section (along with 80 items included in Level 2 for identified participants). Accuracy on trained items is then computed separately.

The assessor presents all the words in the list. For each noun, participants attempt to name the item orally and then write their answer. No feedback is given, as some items serve as generalization items for either P1 or P2. After assessing the nouns, the same procedure is applied to the verbs.

All spoken and written responses are recorded. Spoken responses will be transcribed manually using the International Phonetic Alphabet, and written responses are captured using a smart pen (Symphony Smartpen by Livescribe, n.d.) to ensure accurate data collection. Both the spoken and written responses will be typed into a scoring document.

#### Secondary outcome measures

The secondary outcome measures will be the changes in performance between time points, specifically phonemic accuracy (during spoken naming) and letter accuracy (during spelling) of untrained items. Similar to the primary outcome measure, phonemic and letter accuracy will be calculated on a scale of 0–100%, with higher numbers indicating greater accuracy, using the Phonology analysis and Spelling analysis tools in Open Brain AI (Themistocleous, 2023). The performance on the NaSp spoken naming and spelling task will be used to compute the accuracy of the untrained items.

Additionally, resting-state functional MRI (rs-fMRI) will be used to measure the activity of various brain regions during resting or task-negative conditions. This approach will allow for the evaluation of functional interactions between brain regions. Further details regarding the neuroimaging methods are provided below.

#### Other pre-specified outcome measures

##### Neurocognitive tests

Other pre-specified outcome measures in this trial include neurocognitive tests for broader language and cognitive domains, as well as standardized questionnaires for patient-reported outcome measures (PROM) covering communication and functional abilities.

In particular, we will compute changes in:

##### Language outcomes (for each type of task, corresponding tests are listed):

Oral naming tasks
° Boston Naming Test (BNT) short version (Goodglass and Kaplan, 1983; Mack et al., 1992): a measure of spoken naming abilities for nouns. It provides a total score (score range: min = 0, max = 30; higher score = better outcome) and a total score after phonemic cueing (score range: min = 0, max = 30; higher score = better outcome).° Philadelphia Naming Test-short form A (PNT) (Walker and Schwartz, 2012): a measure of spoken naming abilities for nouns. The test contains 1- and 2-syllable words, as well as low, medium, and high-frequency words. It provides a total score (score range: min = 0, max = 30; higher score = better outcome).° Hopkins Assessment of Action Naming (HANA) (Breining et al., 2022): a measure of spoken naming abilities for verbs. It provides a total score (score range: min = 0, max = 30; higher score = better outcome).° Verb and Sentence Test (VAST) Action Naming (Bastiaanse et al., 2003): a measure of spoken naming abilities for verbs. The test contains transitive and intransitive verbs and low- and high-frequency verbs. It provides a total score (score range: min = 0, max = 40; higher score = better outcome), a high-frequency score (score range: min = 0, max = 19; higher score = better outcome), a low-frequency score (score range: min = 0, max = 21; higher score = better outcome), a transitive verb score (score range: min = 0, max = 29; higher score = better outcome), an intransitive verb score (score range: min = 0, max = 11; higher score = better outcome), a name-related verb score (score range: min = 0, max = 18; higher score = better outcome) and a non-name-related transitive verb score (score range: min = 0, max = 22; higher score = better outcome).Spelling to Dictation
° Johns Hopkins University (JHU) Dysgraphia Battery using the Oral Spelling list (Goodman and Caramazza, 1985): a measure of spelling to dictation abilities. This test contains words and non-words. It provides a total score (score range: min = 0, max = 62; higher score = better outcome), a word score (score range: min = 0, max = 43; higher score = better outcome), a non-word score (score range: min = 0, max = 19; higher score = better outcome) and a letter accuracy score (score range: min = 0, max = 100%; higher score = better outcome).° In-house Spelling to Dictation list: a measure of spelling to dictation abilities. This test contains words from a range of imageability and frequency. It provides a total score (score range: min = 0, max = 30; higher score = better outcome) and a letter accuracy score (score range: min = 0, max = 100%; higher score = better outcome).Morphosyntax Production
° Verb and Sentence Test (VAST) Filling in Finite Sentences (Bastiaanse et al., 2003): a measure of verb retrieval in a finite sentence context. The test contains transitive and intransitive verbs and low- and high-frequency verbs. It provides a total score (score range: min = 0, max = 10; higher score = better outcome).° Verb and Sentence Test (VAST) Filling in Infinite Verbs in Sentences (Bastiaanse et al., 2003): a measure of verb retrieval in an infinite sentence context. The test contains transitive and intransitive verbs and low- and high-frequency verbs. It provides a total score (score range: min = 0, max = 10; higher score = better outcome).° Verb and Sentence Test (VAST) Sentence Construction (Bastiaanse et al., 2003): measures sentence production abilities. The test contains transitive and intransitive verbs and reversible and irreversible verbs. It provides a total score (score range: min = 0, max = 20; higher score = better outcome), an intransitive verb score (score range: min = 0, max = 10; higher score = better outcome), a transitive verb score (score range: min = 0, max = 10; higher score = better outcome), a reversible transitive verb score (score range: min = 0, max = 5; higher score = better outcome), an irreversible transitive verb score (score range: min = 0, max = 5; higher score = better outcome).
Sentence Comprehension
° SOAP sentence comprehension (Love and Oster, 2002): measures sentence comprehension abilities. This task contains four syntactic construction types (matched for length): active, passive, subject-relative, and object-relative, either at the active or passive tense. It provides an active score (score range: min = 0, max = 10; higher score = better outcome), a passive score (score range: min = 0, max = 10; higher score = better outcome), a subject relative score (score range: min = 0, max = 10; higher score = better outcome) and an object relative score (score range: min = 0, max = 10; higher score = better outcome).
Repetition
° Frontotemporal Lobar Degeneration Module (FTLD-MOD) sentence repetition task—extended (Ruch et al., 2022): a measure of repetition abilities. It provides a total score for the original sentences (score range: min = 0, max = 5; higher score = better outcome), a number of omitted words for the original sentences score (score range: min = 0, max= 37, higher score = worse outcome), a number of semantically related or unrelated incorrect real words score for the original sentences (score range: min = 0, max= 37, higher score = worse outcome), a number of phonologically related words or non-words score for the original sentences (score range: min = 0, max= 37, higher score = worse outcome), a total score for the new sentences (score range: min = 0, max = 5; higher score = better outcome), a number of omitted words for the new sentences score (score range: min = 0, max= 63, higher score = worse outcome), a number of semantically related or unrelated incorrect real words score for the new sentences (score range: min = 0, max= 63, higher score = worse outcome), a number of phonologically related words or non-words score for the new sentences (score range: min = 0, max= 63, higher score = worse outcome).
Verbal fluency
° Letter criteria [letter (f, a, and s)]: a measure of verbal fluency abilities (score range min = 0, max = no limits; higher score = better outcome).° Semantic criteria (animals, fruits, and vegetables): a measure of verbal fluency abilities (score range min = 0, max = no limits; higher score = better outcome).
Connected speech:
° Boston Diagnostic Aphasia Examination (BDAE) Cookie Theft (Goodglass and Kaplan, 1983; Goodglass et al., 2001): a measure of oral production. It provides a Correct Information Units (CIU) score (score range: min = 0, max = 8; higher score = better outcome), a total number of words score (score range: min = 0, max = no limits; higher score = better outcome), a ratio of nouns/total number of words (score range: min = 0, max = 1; higher score = better outcome), a ratio of verbs/total number of words (score range: min = 0, max = 1; higher score = better outcome), a ratio of subordinates/number of sentences (score range: min = 0, max = no limits; higher score = better outcome), a ratio of phonological errors/number of words (score range: min = 0, max = 1; higher score = worse outcome), and a ratio of lexico-semantic errors/number of words (score range: min = 0, max = 1; higher score = worse outcome).° Apraxia Battery for Adults (ABA) Circus Scene (Dabul, 2000): a measure of oral production. It provides a CIU score (score range: min = 0, max = 8; higher score = better outcome), a total number of words score (score range: min = 0, max = no limits; higher score = better outcome), a ratio of nouns/total number of words (score range: min = 0, max = 1; higher score = better outcome), a ratio of verbs/total number of words (score range: min = 0, max = 1; higher score = better outcome), a ratio of subordinates/number of sentences (score range: min = 0, max = no limits; higher score = better outcome), a ratio of phonological errors/number of words (score range: min = 0, max = 1; higher score = worse outcome), and a ratio of lexico-semantic errors/number of words (score range: min = 0, max = 1; higher score = worse outcome).° Disease and life events' prompts (Nicholas and Brookshire, 1995): a measure of oral production. It provides a CIU score (score range: min = 0, max = 8; higher score = better outcome), a total number of words score (score range: min = 0, max = no limits; higher score = better outcome), a ratio of nouns/total number of words (score range: min = 0, max = 1; higher score = better outcome), a ratio of verbs/total number of words (score range: min = 0, max = 1; higher score = better outcome), a ratio of subordinates/number of sentences (score range: min = 0, max = no limits; higher score = better outcome), a ratio of phonological errors/number of words (score range: min = 0, max = 1; higher score = worse outcome), and a ratio of lexico-semantic errors/number of words (score range: min = 0, max = 1; higher score = worse outcome).
